## **Recruitment**

Patients are recruited in nine mental health care centers throughout the Netherlands that each agreed on participation with two teams (BAVO Europort, GGZ NHN, GGZ inGeest, Lentis, GGZ Centraal, Antes, Breburg, Altrecht and Arkin). All incoming patients at the participating sites are checked for inclusion criteria by the local staff. Patients meeting the criteria are informed about the study and the RG during intake and asked to participate by the local intaker(s). If patients indicate to be interested, they will receive a patient information brochure and a week time to neutrally consider their participation. They will also be referred to the central researcher for any remaining questions, to ensure that they are fully informed about the nature of the study. Hereafter, the local staff of the FACT-team will contact the patient to inquire whether he/she wants to participate in the study. When the patient verbally agrees with participation the randomization is performed. To this end, the local staff sends a notification email to the central researcher with minimal contact information (surname and telephone number). The central researcher will perform the randomization by entering the following information to the generated allocation list: (1) name of the mental health care center; (2) name of the team; and (3) the sequential number of entry of the new participant. The local researcher will contact the patient to make the first appointment for the baseline measurement. Before start of the baseline measurement, participants sign written informed consent of which they will receive a copy.

In case the number of incoming patients is not enough, patients within the caseload of the trained casemanagers who entered FACT care in the past 12 months will be screened on inclusion criteria and all will be informed about the RG. They will follow the same procedure as described above. The aim is to include as much as possible participants per site, expecting to reach a mean of  $N=10$  per site (ranging from 6 to 14). Recruitment will take place between September 2017 and September 2018, with follow up ending on September 2020.

For both inclusion and follow-up assessments, participants are contacted via the personal information they have provided and approved to use for the study. These entail surname and telephone number. They will be contacted through phone after which they can decide on the location to meet the researcher for the assessments.

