### **Design and Allocation**

The study is a multicenter randomized clinical trial (MRCT), including 180 patients of nine Dutch mental health care centers.

An independent statistician of the Trimbos Institute will generate a computerized allocation list, stratified on mental health care centers and teams. That is, for each team of every mental health care center a separate allocation sequence will be generated by means of allocation blocks assuming a maximum of fourteen participants per team. Two sizes of allocation blocks are used (i.e. 2 and 4), yielding three possible cells (i.e.: 2x4 and 2x2; 1x4 and 5x2; 0x4 and 7x2). These cells in turn, are randomized to keep the allocation unpredictable for the different stakeholders (care-givers and researchers). In order to minimize the risk of imbalance between conditions, the ratio of these possibilities will be stratified on resp. 1:2:2. The allocation sequence will be stored with the independent statistician and is concealed from all researchers, caregivers, and participants. Once allocated, condition is passed on to the central researcher and local staff by email so that the local intake procedure can be continued. Further matching between patient and case manager is allowed and performed by the local staff of the FACT-team. At start of the baseline measurement (0 months), written informed consent is obtained. Further assessments take place 9 (T1) and 18 (T2) months after obtaining informed consent.. Local independent research assistants will carry out all assessments. Assessments comprise self-report questionnaires (administered on PC) and interviews, see Table 1 and Table 2. Given the nature of our study, blinding of participants and treating clinicians is not possible. The local research assistants however are blinded. To optimize similarity in assessments, research assistants use an extensive standardized study protocol and discuss process in regular telephonic and face-to-face meetings with the central researcher.

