## STATISTICAL ANALYSES:

### Effectiveness RG

Data will be analyzed according to the "intention to treat" principle, including all patients regardless of whether they drop out from treatment or not (StataSE 12.1). We will use Student's t-tests for continuous variables and Pearson chi-squared tests for categorical variables to analyze potential between-condition differences in baseline characteristics. Variables that show different distributions in the conditions, and are correlated with the results, are included in the analysis as a covariate. We will use pre-specified cut-off points of the RG model fidelity checklist to define good adherence.

Primary outcome (empowerment) and secondary outcome parameters are analyzed by means of multilevel mixed regression models with 4 levels: observations within persons, persons within teams and teams within centers. Baseline values of the parameters will be included in the model in order to control for regression to the mean. For categorical outcome variables, counts and in case of non-normal residuals, appropriate forms of mixed regression will be chosen (binomial,

Poisson, gamma, etc). Results are described in accordance with the CONSORT guidelines for randomized controlled trials (Schulz, Altman & Moher, 2010).

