### **SUBJECT BURDEN**

Subjects in both conditions are asked to participate in the three assessment appointments, 0, 9 and 18 months after giving informed consent. The assessments take 1,5 to 2 hours and consist of self-report questionnaires and interviews, guided by the research-assistant. When the research-assistant notices that this is too long for the participant (decreased concentration, fatigue, symptoms) the appointment may continue at another time. Data collection for RG-members (experimental condition) and significant others (control condition) is provided via mail with an online questionnaire. Moreover, in the experimental RG-condition subjects are asked to prepare, attend and evaluate the RG-meetings.

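### Patients are randomised, and the result goes to unblinded staff, before written consent and baseline, so trial entry and the self-rated baseline covariate can depend on the arm

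*Protocol*

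**What the plan says.** Two sections of the protocol give the order of events, and they agree on it.

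- **Recruitment.** Patients are told about the study and the Resource Group (RG), receive a brochure and have a week to consider. Then: "When the patient verbally agrees with participation the randomization is performed". After that, "The local researcher will contact the patient to make the first appointment for the baseline measurement". The consent form is signed at that visit, before the measurements begin.
- **Design and Allocation.** "Once allocated, condition is passed on to the central researcher and local staff by email so that the local intake procedure can be continued". Staff then act on the result: "Further matching between patient and case manager is allowed and performed by the local staff of the FACT-team". On consent: "At start of the baseline measurement (0 months), written informed consent is obtained". Participants and treating clinicians are not blinded; the research assistants are.

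The primary outcome, the Netherlands Empowerment List (NEL), is listed in Table 1 as self-rated. Under Effectiveness RG, the primary model uses its baseline value: "Baseline values of the parameters will be included in the model in order to control for regression to the mean". The intention-to-treat sentence in the same section deals with patients who stop treatment. It does not mention patients who are randomised and never sign.

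**The concern.** Randomisation protects the comparison only if everything that defines the trial population and its covariates is fixed before the arm is known. Here two such things come afterwards.

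1. **Entry.** Patients know about the RG when they agree verbally. Someone who learns of an unwanted allocation can decline to sign. That person has been randomised but contributes no data, and the intention-to-treat wording does not cover the case.
2. **The covariate.** The baseline NEL is self-rated after allocation. If knowing the arm changes how a patient answers, adjusting for that baseline carries the change into the estimated treatment effect.

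A concealed sequence protects the assignment up to the moment of allocation. Blinded assistants protect observer ratings. Neither protects the interval between allocation and signature, or a self-rated scale.

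**Working it through.** **Order of events, from Recruitment and from Design and Allocation**

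1. Information and one week to consider
2. Verbal agreement
3. Randomisation
4. Allocation e-mailed to the central researcher and local staff; intake continues; patient and case manager are matched
5. Appointment for the baseline visit
6. Written consent
7. Baseline assessment, including the NEL

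Steps 6 and 7 should come before step 3. The protocol does not say when the patient is told the arm. Unblinded staff hold it from step 4, and no provision withholds it from the patient until after step 7.

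**Inputs from Sample size.** Planned effect d = 0.5; two-sided level 0.05; power 80%; 63 per condition; within-person correlation 0.6; 133 patients needed before the drop-out allowance.

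**Yardstick.** n per arm = 2 × (1.96 + 0.84)² / 0.5² ≈ 63, so the plan's own figure reproduces. The effect of 0.5 SD serves as the scale below.

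**Covariate route (assumed shift).** Take the baseline slope as 0.6, equal to the within-person correlation, and suppose the shift is confined to baseline.

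Bias of the adjusted effect = −0.6 × (arm-induced difference in baseline)

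For the type I error, assume 133 analysed 1:1, one follow-up and no clustering. The residual SD is √(1 − 0.6²) = 0.8 and the standard error is 0.8 × √(2/66.5) = 0.139.

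| Assumed baseline shift (SD) | Size of bias (SD) | Share of d = 0.5 | Type I error |
|---|---|---|---|
| 0.05 | 0.03 | 6% | 5.5% |
| 0.10 | 0.06 | 12% | 7.2% |
| 0.20 | 0.12 | 24% | 13.9% |
| 0.30 | 0.18 | 36% | 25.4% |

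The bias is opposite in sign to the shift. A raised baseline in the RG arm, or a lowered one in the control arm, makes the RG effect look smaller. The reverse shifts make it look larger.

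**Selection route (assumed refusals).** Suppose 15% of one arm and 5% of the other do not sign.

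- Decliners 0.5 SD below the overall mean: 0.5 × (0.15/0.85 − 0.05/0.95) = 0.062 SD between arms.
- Decliners 0.5 SD below those who sign: 0.5 × (0.15 − 0.05) = 0.05 SD.

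Baseline adjustment removes all of this if selection acts only through the baseline score. If the difference persists fully to follow-up, what remains is 0.062 × (1 − 0.6) ≈ 0.025 SD, or 0.05 × (1 − 0.6) = 0.02 SD. That is 4 to 5% of the planned effect.

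**The case against.** The strongest reply is that the link to bias is inferred. The allocation goes to the central researcher and local staff, not to the patient, and both routes need the patient to know or sense the arm before signing or completing the NEL. Fig 1, on the randomisation and assessment procedure, was not available here and might settle this. This stands: the text supports *can depend*, not *did depend*.

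There are also mitigations. A brochure, a week to consider and access to the central researcher should make late refusals less common. The protocol also says the content of treatment differs little between arms. These reduce the risk but do not close the gap.

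A reader might go further in four ways that the documents do not support.

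- **That the mixed model can repair nothing.** Baseline adjustment removes part, possibly all, of a selection shift. It is the covariate route that adjustment itself creates.
- **That the gap between 180 planned and 158 in the final sample shows patients lost after allocation.** The list of changes does not say whether 158 counts randomised or consented patients.
- **That concealment failed.** Design and Allocation places the sequence with an independent statistician, while Recruitment says "The central researcher will perform the randomization by entering the following information to the generated allocation list". The two statements should be reconciled, but they do not show that anyone saw the list in advance.
- **That the EQ-5D and the caregiver questionnaire (BES) are further instances.** Correction for baseline utilities appears only as a sensitivity analysis in the economic evaluation. The BES is listed among additional measures and does not enter the NEL analysis.

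**Conclusion.** The concern holds as a weakness in the order of procedures. As written, randomisation and release of the allocation to unblinded staff come before written consent and before the baseline NEL used in the primary model. Entry and the covariate can therefore depend on the arm, and the intention-to-treat wording does not deal with patients who are randomised and do not sign.

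The order is certain; the size is not. The figures of 0.06 to 0.12 SD (covariate) and about 0.02 to 0.025 SD (selection, after adjustment) rest on assumed shifts and refusal rates, and on a slope set equal to the plan's within-person correlation. The direction cannot be fixed in advance, and some plausible shifts would work against the trial's hypothesis. Nothing in the protocol shows that bias occurred.

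**What to change.** **Procedure.** In Recruitment, in Design and Allocation and, where needed, in Fig 1, put the steps in this order: written consent, baseline assessment, randomisation, release of the allocation to local staff. Define the intention-to-treat set as all patients randomised. The steps themselves do not change and no sample-size figure moves. The cost is that staff learn the arm somewhat later.

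**This trial.** The list of changes reports a final sample and the 18-month measurements, so reordering cannot help patients already randomised. For them:

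- report by arm the number randomised, the number who did not sign or had no baseline, and the reasons;
- compare baseline NEL by arm;
- add a sensitivity analysis of the primary outcome without baseline adjustment.

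The unadjusted analysis is free of the covariate route but keeps the full selection shift, so it should be read beside the adjusted one and not in place of it. It is also less precise: with a slope of 0.6, the standard error is larger by a factor of 1/0.8 = 1.25. These reports do not undo the design weakness, but they let readers judge how much it could matter.

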## **INTERVENTION**

### **Experimental group: FACT care as usual + Resource Groups**

Patients will receive FACT care as usual. Next to this, they are guided to form their own Resource Group (RG) with whom they will meet on average once every three months. They are asked to prepare, attend and evaluate the RG meetings. The central element in the RG is the patient as the director of the group (Nordén et al., 2012b). That is, the patient nominates group-members sets his/her self-recovery treatment goals and decides on the location and time of the meetings, guided and supported by the case manager (CM). The CM and the patient always take part of every RG meeting, and the psychiatrist of the FACT-team attends the RG once a year if possible and necessary. Other RG-members can be significant others (family members, friends or others) as well as (family) experts and professionals from within and outside mental health care. The recovery goals can relate to all aspects of recovery, such as personal recovery (recovery of identity), social rehabilitation (meaningful participation and performance in society) and health (treating and improve physical and mental symptoms). During the meetings, the group decides on the role of each member in accomplishing the intended goal. The RG makes decisions together and takes responsibility for seeing to it that the development plan is followed (Nordén et al., 2012b). All the RG-meetings are clearly and consistently structured over time and follow the agenda that the patient and the CM agreed on. Additionally, an action plan for recognizing early warning signs that indicate an approaching relapse is established so that RG members can provide adequate, adjusted guidance that is designed and approved by the patient. Between the meetings and during evaluation, subjects are motivated to work on these goals and to involve the RG members in this process.

The CM coordinates the implementation of the RG and bears responsibility for monitoring that the RG method is carried out as intended. Moreover, the CM invites the nominated RG members for an interview before the first RG-meeting to explore the possible RG-participation as well as the relation between the nominated member and the patient. The purpose of these interviews is to give space to the story and the experiences of all RG-members. Also, there is attention to express possibly existing emotions towards the patient and/or other members of the RG so that the so called 'expressed emotions (EE)' are low during the RG meetings. Hereby, the CM has a key-role in creating a good emotional environment around the patient. Additionally, the CM can train the patient and the RG-members in- or outside the RG meetings when he/she notices structural problems within the group- for example emotional communication, handling stress, conflicts between members, inadequate knowledge about the mental disease or a lack of problem-solving skills, or suggest to invite a colleague into the RG to help with this. This way, maladaptive patterns can be addressed in order to remove the barriers that are blocking the way to a successful resource group. Alternatively, the CM can decide to involve an expert, for example in family therapy, for an extra session for (part of) the RG when more complex problems are evident.

Taken together, the CM facilitates a gradual transfer of personal responsibility to the client. That is, it is the client who is to be given influence and it is the task of the CM to give the client support and the tools to be able to take the power to carry that responsibility.

### **Comparison group: FACT care as usual**

In the comparison group, patients will receive FACT care as usual. Importantly, patients in this group are also motivated to work on their treatment goals. Moreover, as is regular practice in FACT care, significant others are involved in the treatment and structural problems between patients and their significant others are addressed. However, these aspects are not to be handled according to the structure of the RG-method.

### **Case managers, training and model fidelity**

At least two members from each FACT team receive an extensive 2-day training program before study start and two follow-up afternoons during the course of the study. Moreover, yearly booster sessions are organized. Two experienced and skilled trainers lead the interactive trainings. The program consists of lectures, role-plays and discussions to study and familiarize the vision, methodology and the content of the roles within the RG-approach. The central element during these days is to habituate on transferring the “guidance” to the patient and his chosen RG in order to nourish the patient’s confidence to reach his or her own goals.

Adherence to the RG protocol is assessed using a RG model fidelity scale. Based on the RG handbook and Swedish material, the scale will be developed to estimate the extent to which the resource groups operate according the intended approach. A first draft of the scale will be presented to involved researchers, (peer)experts and representatives of the participating sites. After modifications, the scale is tested at two of the participating sites. Based on the experiences, the scale will be adjusted if necessary and the final version will be implemented at all sites. After 9 and 18 months, an external auditor will score all the RG’s on the model fidelity together with the CM so that for each RG a model-fidelity score is obtained. Moreover, the control condition will be scored on model fidelity at 9 and 18 months. Part of the list is a logbook that case managers fill in after each RG-meeting (only for experimental condition). The logbook consists of 7-10 questions, answered online. The central researcher will go through the answers and can hereby assess (1) whether RG-meetings take place; and (2) whether the RG-meetings are accomplished according to the RG-method.

Moreover, trained case managers will attend peer-to-peer coaching sessions. These are telephone group sessions of 1h – 1.5h once every 8 weeks in a set group of max 8 case managers from different institutions/regions. The sessions will also be attended by the central researcher, allowing to keep track of recurrent themes and the quality of the session.

The central researcher will perform frequent visits to each participating team during the course of the study. The purpose of these work visits is to evaluate the RG approach in Dutch clinical practice and identify obstacles and improvements during implementation. Additionally, the trained case managers within a team meet once every two weeks with each other to discuss the different RG-group cases. Any recurrent questions/themes will be discussed with the central researcher, and if necessary with the trainers.

### **STUDY PARAMETERS (PRIMARY AND SECONDARY STUDY OUTCOMES)**

Several questionnaires will be administered in order to assess recovery. To operationalize the concept of recovery, a three dimensional framework will be adapted (Couwenbergh et al., 2014):

- 1) Personal recovery.** Defined as a highly personal process in which a patient can give meaning to previous events and steps are taken to regain grip at one’s life (Stel, Stringer, & Koene, 2015). Personal recovery can be reached even if there are still (severe) clinical symptoms present (Wunderink, Nieboer, Wiersma, Sytma, & Nienhuis, 2013).
- 2) Societal recovery.** Patients often experience social exclusion and broken relations with family and friends (Whitley & Drake, 2010). Societal recovery aims to degrade the public stigma on mental illness and improve the position and rights of (ex-)patients within society (Couwenbergh et al., 2014). Furthermore, it entails improvement in housing, work, education and social relations (Stel, 2012).

3) *Clinical recovery* is the traditional aim in mental health care, striving to decrease the presence of symptoms and to increase one's physical functioning (Huber et al., 2016).

**Primary outcome parameter:**

*Personal recovery:*

Empowerment will be assessed with the '*Nederlandse Empowerment Lijst*' (NEL; Boevink, Kroon, Delespaul & Os, van, 2017) containing 6 subscales: confidence and purpose, social support, connectedness, self-management, caring community and professional help. This questionnaire is selected because the domains closely match the outcomes that are expected from the RG-method. The list was established in collaboration with patients and experts-by-experience and is frequently used in evaluations inside and outside the Dutch Mental Health Care. Internal consistency (Cronbach's alpha = 0.94 total score; subscales ranging from 0.74 to 0.90), aspects of validity, reproducibility (intraclass correlation = 0.79) and responsiveness were good (Boevink et al., 2017). This was confirmed by Van Gestel-Timmermans and colleagues (2012). In trials, sensitivity to change has been shown (Van Gestel-Timmermans, Brouwers, Van Assen & Van Nieuwenhuizen, 2012; Michon, Wezep, van, Rijkaart, Overweg, Vink & Kroon, 2013).

